**12. Outcomes**

**Main outcome**

**Efficacy of auricular acupuncture:** The blood pressure will be measured at baseline, 4 weeks and 8 weeks after allocation. The efficacy of auricular acupuncture is defined as office diastolic blood pressure is reduced to a threshold set out in “Guiding Principles for Clinical Research of New Chinese Medicines” formulated by the Ministry of Health of the Peoples Republic of China a significant effect means a diastolic blood pressure decrease ≥10 mmHg and return to normal level or a decrease ≥ 20 mmHg. An effect means a diastolic blood pressure decrease <10 mmHg and return to normal level or decrease of 10 to 20 mmHg. Invalid means that the change in blood pressure did not reach the “effect” level described above.

Requirements for blood pressure measurement:

(1) blood pressure will be measured in the afternoon and in a quiet room with comfortable temperature (22℃-24℃) by one well-trained researcher.

(2) use validated upper-arm cuff device and sphygmomanometer for blood pressure measurement, and ensure the calibration before the measurement.

(3) Before measurements: remain seated and relaxed for at least 5 min; avoid smoking, caffeine and exercise for 30 min; empty bladder.

(4) Sit in a backrest chair with back supported on chair, legs uncrossed and feet flat on floor, arm resting on table with mid-arm at heart level.

(5) Tie the cuff to the upper arm, and tighten it so that it can be inserted 1 to 2 fingers. The lower edge of the cuff should be 2.5cm above the elbow fossa.

(6) Blood pressure of both upper arms is measured at first visit and the higher side is usually measured later. At each visit take 2 measurements with 1-2 min between them. Calculate the average of the 2 measurements. If the 2 readings of systolic or diastolic blood pressure varied by more than 10mmHg, the third time is taken and the average of the last two measurements is recorded.

**Secondary outcomes**

(1) **PDC score:** Patients’ PDC score will be determined by TCM physicians using the TCM Constitution Scale compiled by [name] in 2009. This scale consists of nine subscales. The original score of the PDC subscale is equal to the sum of the scores for each item, and the transformed score is calculated as follows: [(original score - number of items)/(number of items × 4)] ×100. PDC score will be measured at baseline, 4 weeks and 8 weeks after allocation, and the transformed score will be recorded.

(2) **Proteins of the RAS** **ACE、AngⅡ、ACE2、Ang (1-7):** Serum concentrations of ACE, AngⅡ, ACE2, Ang (1-7) will be tested using enzyme-linked immunosorbent assay. The participants will be required to avoid drinking alcohol and intense exercising one day before sample collection. Females should avoid having their menstrual period during collection. Serum will be separated from the blood by centrifugation and will be stored at -80℃ until final analysis. Blood sample will be collected from each eligible participant at baseline and 8 weeks after allocation.

**(3) Office blood pressure of different genotypes:** Only participants in the intervention group will have gene polymorphism testing at baseline. Five single nucleotide polymorphisms (ACE, ACE2, AT1R, AT2R, Mas) will be genotyped by mass spectrometry or polymerase chain reaction. The changes in office blood pressure of different genotypes will be analyzed to determine whether genotype influence the blood pressure-decreasing response to antihypertensive treatment with auricular acupuncture.

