**4. Trial process chart**

| Outcomes | Evaluation time | | |
| --- | --- | --- | --- |
|  | Baseline | 4 weeks after allocation | 8 weeks after allocation |
| Blood pressure | × | × | × |
| phlegm-dampness constitution score | × | × | × |
| Proteins of the RAS | × |  | × |
| Gene polymorphism testing (only intervention group) | × |  |  |

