**6. Research purposes**

(1) The changes of proteins of the RAS before and after auricular acupuncture will be compared to explore the mechanism underlying the effect of auricular acupuncture on blood pressure.

(2) Participants in the intervention group will have gene polymorphism testing, the changes in blood pressure of different genotypes will be analyzed to determine whether genotype influence the blood pressure-decreasing response to antihypertensive treatment with auricular acupuncture. And to identify genes of RAS that are sensitive to auricular acupuncture.

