**8. Study design**

Randomized controlled trial, parallel

[figure not shown]

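### Genotyping the intervention arm alone supports a within-arm association, not the claim that genotype influences the response to auricular acupuncture

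*Protocol*

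**What the plan says.** Section 6 of the protocol gives two purposes. The second is to genotype the intervention group and compare blood pressure changes between genotypes "to determine whether genotype influence the blood pressure-decreasing response to antihypertensive treatment with auricular acupuncture". It continues: "And to identify genes of RAS that are sensitive to auricular acupuncture".

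Section 12, secondary outcome (3), puts this into practice: "Only participants in the intervention group will have gene polymorphism testing at baseline". The panel is fixed: "Five single nucleotide polymorphisms (ACE, ACE2, AT1R, AT2R, Mas) will be genotyped by mass spectrometry or polymerase chain reaction". The analysis is described in one sentence, beginning "The changes in office blood pressure of different genotypes will be analyzed", and the same aim of determining an influence on response is repeated there. The process chart in section 4 carries the same restriction to the intervention group.

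The design in section 8 is "Randomized controlled trial, parallel", and the chart schedules blood pressure at baseline, week 4 and week 8 without limiting it to one group. For the RAS proteins, secondary outcome (2) says "Blood sample will be collected from each eligible participant at baseline and 8 weeks after allocation". No section provides for genotyping controls or for an arm-by-genotype comparison, and none describes the genotype objective as exploratory.

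**The concern.** Purpose 2 is a statement about effect modification: that the benefit of acupuncture over control differs by genotype. Answering it needs the genotype contrast in both arms. The plan yields the contrast in one arm only. That contrast also contains any difference between genotypes in eight-week blood pressure change that would have occurred without acupuncture.

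Genotype is not randomised, so a comparison of genotypes within one arm is observational. The randomised control arm is what would separate the two components, and it is not genotyped. A later analysis plan cannot repair this, because what is missing is data and not a method.

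At stake is the second of the trial's two purposes. Section 5 says its result is meant as a reference for improving the efficacy of auricular acupuncture. A genotype that only tracks blood pressure change in general could be reported as one that is sensitive to acupuncture.

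**Working it through.** **1. What the planned contrast estimates.** Let T(g) and C(g) be the mean blood pressure change in treated and control participants with genotype g (1 = carrier, 0 = non-carrier).

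- Prognostic part: P = C(1) − C(0).
- Effect modification: M = [T(1) − C(1)] − [T(0) − C(0)].
- Planned within-arm contrast: T(1) − T(0) = P + M.

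Purpose 2 concerns M. The trial observes P + M and has no estimate of P. No sample size or model separates them, and this step needs no assumed numbers.

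**2. The plan's own figure.** The only sample size stated is for the main efficacy rate (section 9: 28% against 0%, α 0.05, β 0.10). With mean proportion 0.14 and two-sided α, n = 2 × 0.14 × 0.86 × (1.960 + 1.282)² / 0.28² = 32.3, so 33 per group. 33 × 1.2 = 39.6, so 40. The stated 40 per group reproduces. It has no bearing on the genotype objective, for which no figure is given.

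**3. Conditional illustration in mmHg.** Inputs:

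- Completers in the treated arm: 40 × 0.8 = 32 (section 9).
- Two genotype groups of 16: assumed.
- SD of diastolic change 8 mmHg: assumed; the protocol gives none.
- M = 0, so there is no effect modification at all.

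SE = 8 × √(1/16 + 1/16) = 2.83 mmHg, with 30 degrees of freedom. The two-sided t test at 0.05 then rejects as follows.

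| Purely prognostic shift (mmHg) | Shift / SE | Probability of p < 0.05 |
| --- | --- | --- |
| 2 | 0.71 | 11% |
| 3 | 1.06 | 18% |
| 5 | 1.77 | 40% |
| 6 | 2.12 | 54% |

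**4. The same comparison in SD units, by simulation** (40,000 trials per scenario, 40 per arm, carrier share 50%, both assumed).

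| True situation | Planned within-arm test | Interaction test, both arms genotyped |
| --- | --- | --- |
| P = 0.8, M = 0 | 68% | 5% |
| P = 0, M = 0.8 | 68% | 41% |
| P = 0.8, M = −0.8 | 5% | 42% |

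The planned test gives the same answer for pure prognosis and pure modification. It also misses real modification when the two cancel.

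**5. The price of the interaction test.** Its SE is √2 times the within-arm SE. With equal genotype groups, the modification detectable with 80% power (normal approximation) is 2.80 × √(4/40) × √2 = 1.25 SD at 40 per arm, and 2.80 × √(4/32) × √2 = 1.40 SD at 32 per arm. With an SD of 8 mmHg these are about 10 and 11 mmHg.

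**The case against.** The best defence is that the previous study in section 9 had a control efficacy rate of 0%, so the prognostic part might be negligible. That does not follow. It is a responder rate on a threshold definition. It is compatible with a mean change in controls other than zero, and with changes of a few mmHg that differ by genotype.

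A second defence is that the aim is modest: section 5 calls the idea speculation and its result a reference. That softens the tone, but sections 6 and 12 still say the comparison will determine an influence on response, and section 6 adds the identification of sensitive genes.

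Four stronger readings are tempting, and the protocol does not support them.

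- A reader might infer that the genotype data are of no use. They are not: an association among treated participants can be estimated.
- A reader might infer from section 5 that the authors themselves expect genotype to act through permitted background drugs. Section 5 does state in general terms that polymorphisms determine drug effect. However, its three examples are all angiotensin receptor blockers, and section 7 excludes participants taking them. A stable background drug may also affect the level of blood pressure without affecting its eight-week change.
- A reader might infer that regression to the mean inflates the error rate whenever genotypes differ at baseline. With an assumed 5 mmHg baseline difference, SD 9 and correlation 0.6, rejection is about 10% only if both genotypes regress to one common mean. If the difference is a fixed property of genotype and persists, it is about 5%. The point does not rest on this.
- A reader might infer that control DNA is already in hand because blood is taken from everyone. Section 12 describes only serum preparation, and section 20 adds only labelling and storage. Whether DNA can be obtained, and whether controls consent to genetic testing, cannot be seen here.

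It also stands that the mmHg figures presuppose a prognostic effect; nothing in the protocol shows that one exists or how large it would be.

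**Conclusion.** The concern holds for the acupuncture-specific claim. As designed, the trial can describe how blood pressure change varies with RAS genotype among treated participants. It cannot show that genotype influences the response to acupuncture, nor that a gene is sensitive to it. This follows from genotyping one arm and depends on no assumed figure.

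The size of the resulting error is conditional. Under the assumptions stated (16 against 16, SD 8 mmHg), purely prognostic shifts of 2 to 6 mmHg would be declared significant in about 11% to 54% of trials, against a nominal 5%.

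The scope is limited: one of two stated purposes, carried by a secondary outcome. The primary efficacy comparison between randomised arms and the RAS protein outcome are not affected. The wording should still be corrected, because the conclusion it promises would not follow from the data collected.

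**What to change.** **Needed: wording only.** In section 6, restate purpose 2 as an exploratory association of RAS genotype with blood pressure change among participants receiving auricular acupuncture, and delete the aim of identifying sensitive genes. Make the same change to secondary outcome (3) in section 12, and word the eventual conclusion accordingly. This costs nothing in assays, visits or participants.

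**Optional: genotype the control arm as well.** This depends on confirming that DNA can be obtained from control participants and that their consent covers genetic testing. Week-8 diastolic pressure would then be modelled on arm, genotype, arm-by-genotype and baseline diastolic pressure, and purpose 2 would rest on the interaction with its confidence interval. The cost is about 40 more samples on the five-polymorphism panel, and possibly an additional sample from controls. This makes the question answerable in principle but not precisely: only modifications of about 1.25 SD or more would be detectable with 80% power at 40 per arm. Five polymorphisms each tested at 0.05 would also carry a family-wise error of 1 − 0.95⁵ = 23% if independent. The result should therefore be labelled exploratory under this option too.

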**4. Genotypes may affect the sensitivity of EH patients with PDC to auricular acupuncture.**

By summarizing the existing clinical research literature, it have found that auricular acupuncture can reduce blood pressure and improve related symptoms, but some patients are not sensitive to auricular acupuncture in many researches. Furthermore, multiple studies have shown that antihypertensive drug efficacy is associated with the gene polymorphism of RAS. Huang Hong’s study showed that In EH patients with different genotypes of ACE gene, the antihypertensive efficacy of irbesartan and the reduction of plasma RAS activity before and after irbesartan treatment were different, manifested as DD > ID > II, which shows that the ACE I/D polymorphism may be an important indicator affecting the antihypertensive response to irbesartan in EH patients. Gong Hongtao using polymerase chain reaction to analyze AT_1_R genes 1166A/C, -810A/T and -521C/T polymorphism of the patients, The results showed a significant difference in the comparison of diastolic blood pressure drop before and after using telmisartan between the AT_1_R gene -521C/T CC genotype and CT + TT genotype (P<0.05), it showed that the -521C/T polymorphism of AT_1_R gene can independently predict the individual difference in patients' response to telmisartan. Men Chen investigated the relationship of A1675G gene polymorphism of AT_2_R and antihypertensive efficacy of losartan in EH patients, found that A allele may be the key factor influencing the antihypertensive efficacy of losartan. In conclusion, gene polymorphisms determine the differences in the effect of antihypertensive drugs, resulting in individual differences in the effect of drug treatment. Therefore, it is speculated that gene polymorphisms may also affect the effect of auricular acupuncture, but no relevant study has reported the relationship between the effect of EH and auricular acupuncture in patients with different genotypes. This study intends to test the polymorphisms of key genes of RAS in EH patients with PDC, analyze the sensitivity of different genotypes and alleles to auricular acupuncture, and provide a reference for improving the efficacy of auricular acupuncture.

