**9. Sample size calculation**

The sample size for this RCT has been computed based on our previous study (36). In our previous study, the efficacy rate was 28% in the intervention group and 0% in the control group after eight weeks of auricular acupuncture intervention. Setting an α-value of 0.05 and a β-value of 0.10, the sample size was calculated using the following formula:

$$n=\frac{{2\bar{p}\bar{q}\left( z_{\alpha}+z_{\beta} \right)}^{2}}{\left( p_{1}-p_{2} \right)^{2}}$$

Considering a dropout rate of 20% during the research, a total of 40 participants per group will be enrolled in the study, for a total required sample size of 80.

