**18. Statistical analysis**

The statistician will use SPSS 25.0 software to analyze the data; a *P*-value < 0.05 will be considered statistically significant. Continuous variables will be expressed as means and standard deviations, or as medians and interquartile ranges. Categorical variables will be expressed as frequencies. Continuous variables will be analyzed by *t* tests or Wilcoxon rank-sum tests. The difference before and after treatment in each group will be determined using a paired *t* test. A chi-squared or Fisher’s exact test will be used to compare the efficiency between the intervention and control groups.

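### Testing five polymorphisms at an unadjusted P < 0.05 in at most 40 people gives about a 23% chance of naming a sensitive gene when none exists

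*Protocol*

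**What the plan says.** Protocol section 12, Secondary outcomes (3), states: "Only participants in the intervention group will have gene polymorphism testing at baseline". It continues: "Five single nucleotide polymorphisms (ACE, ACE2, AT1R, AT2R, Mas) will be genotyped by mass spectrometry or polymerase chain reaction". Changes in office blood pressure are then compared between genotypes. The item does not say whether systolic pressure, diastolic pressure or both are meant, nor which of the two follow-up visits (weeks 4 and 8) counts.

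Section 5, part 4, gives the intention to "analyze the sensitivity of different genotypes and alleles to auricular acupuncture". Section 6 (2) adds the purpose: "And to identify genes of RAS that are sensitive to auricular acupuncture". None of these places calls the analysis exploratory.

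Section 9 plans that "a total of 40 participants per group will be enrolled in the study, for a total required sample size of 80". That figure is derived from the efficacy rate of the main outcome. Section 18 sets one general rule, a P-"value < 0.05 will be considered statistically significant". For continuous variables it lists t tests or Wilcoxon rank-sum tests, plus a paired t test within each group. It assigns no test to the genotype outcome by name.

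**The concern.** An aim to identify genes needs a decision rule that seldom names one by chance. Here the rule is the ordinary 0.05 level, applied to a family of at least five hypotheses in a sample sized for a different question.

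The between-group tests listed for continuous variables compare two groups. The protocol's background gives one example with three genotypes (DD, ID, II) and another that is already pooled into two (CC versus CT + TT). How many comparisons each polymorphism will generate is therefore open, and each extra one raises the error rate.

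At stake is one of the trial's two stated purposes. The main comparison between arms is not affected.

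**Working it through.** **Inputs.** Five polymorphisms, intervention arm only (section 12). 40 per group and 20% dropout (section 9). Threshold 0.05 (section 18). Allele frequencies, the SBP-DBP correlation and effect sizes are not in the protocol; the values below are assumptions.

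**The plan's own figure.** With p1 = 0.28, p2 = 0, mean p = 0.14, two-sided α = 0.05 and 90% power, the protocol's formula gives n = 2 × 0.14 × 0.86 × (1.960 + 1.282)² / 0.28² = 32.3, so 33. Then 33 × 1.2 = 39.6, so 40. The stated 40 is reproduced, but it sizes the efficacy comparison only. The genotyped sample is at most 40, or 40 × 0.8 = 32 completers.

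**Chance of at least one false positive when no gene matters.** For k independent tests this is 1 − 0.95^k.

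| Reading | k | Independent | Null simulation |
|---|---|---|---|
| One two-group test per polymorphism | 5 | 22.6% | 22–24% |
| The same, on both SBP and DBP | 10 | 40.1% | 37–38% |
| All pairs of three genotypes, one pressure | 15 | 53.7% | 42–47% |

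The simulation used 2,000 runs per setting, n = 32 or 40, independent loci, minor allele frequency 0.3 or 0.5, and an SBP-DBP correlation of 0.6. The first row is the minimum family that the protocol implies. The other two are readings it leaves open.

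**After adjustment.** Bonferroni gives 0.05 / 5 = 0.01 per polymorphism. The family-wise error is then 1 − 0.99⁵ = 4.9%.

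**Power.** For a two-group contrast, power ≈ Φ(d × √(n₁n₂/N) − z).
- 40 people split 20/20, d = 0.8 SD: 0.8 × √10 = 2.53. At 0.05, Φ(2.53 − 1.96) = 72%. At 0.01, Φ(2.53 − 2.576) = 48%.
- 32 people split 16/16, d = 0.8 SD: 62% at 0.05 and 38% at 0.01.
- 40 people split 20/20, d = 0.5 SD, unadjusted: 35%. With a 10/90 split: 16%.
- Smallest difference detectable with 80% power, 20/20 split: (1.960 + 0.842) × √(1/20 + 1/20) = 0.89 SD at 0.05, and (2.576 + 0.842) × √(1/20 + 1/20) = 1.08 SD at 0.01.

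**The case against.** The best defence is that this is the last-listed secondary outcome, that the background presents the gene effect as speculation meant to provide a reference, and that multiplicity and the genetic model are often left to a statistical analysis plan, which is not shown here. Part of this stands. The missing detail is not in itself an error, and the absence of a baseline covariate is not one either, since changes from baseline are already analysed. What remains is what the protocol does state: five loci, a 0.05 rule and an aim to identify genes, without an exploratory label.

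Some stronger readings are tempting, but the documents do not support them:
- **A false gene claim is more likely than not.** A reader might reach this by counting both pressures at both visits, or all genotype pairs on both pressures, with every P-value treated as a possible claim. The protocol prescribes neither, and positive correlation lowers figures that assume independence.
- **Two-group tests are fixed for the genotype outcome.** This is an inference from the only tests listed for continuous variables.
- **Genotypes will be pooled after the data are seen.** Nothing says so. The background itself cites a two-group contrast, and such a contrast can be set in advance.
- **About 23% of declared genes would be false.** The 23% is the chance of at least one false claim when no gene matters. The share of claims that are false depends on how many genes truly matter: with 35% power it is about 56% if 10% do (0.045 / 0.080) and about 13% if half do (0.025 / 0.200).

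**Conclusion.** The point holds in a limited form. On the narrowest reading, the stated rule carries about a 23% chance of a false gene claim, more than four times the nominal 5%. This assumes independent loci and one test per polymorphism. If both pressures are tested it is about 37 to 40%, and it rises further if both visits or all genotype pairs are used.

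In 32 to 40 people, power for moderate effects is also low. A declared gene would therefore be weak evidence, and a gene that is not declared would not thereby be shown to be irrelevant. Adjusting the threshold corrects the error rate but does not make the sample adequate for identifying genes.

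**What to change.** Choose one of two routes and write it down before the data are analysed.

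1. **Adjusted test.** Name one pressure, one visit and one genetic coding for each polymorphism; week-8 DBP would be in line with the main outcome. Fit a linear model for each polymorphism with baseline pressure as a covariate. Declare a gene only if it passes Holm, or Bonferroni at 0.01, across the five.
2. **Exploratory label.** Call the analysis exploratory, replace the aim of identifying genes with one of estimating differences by genotype, and report estimates with confidence intervals.

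On either route, report the other pressure, the other visit, allele comparisons and alternative codings descriptively, and soften the conclusion in section 6.

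The cost is wording and a slightly different model, using data that are already to be collected. The price of the first route is the loss of power shown above, from about 72% to 48% for a 0.8 SD difference with 40 people split evenly. The price of the second is that the trial no longer claims to name sensitive genes.

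### Genotypes are compared on the raw change in office blood pressure with unadjusted tests, although baseline is measured: precision is lost and a chance baseline gap can colour the result

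*Protocol*

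**What the plan says.** Protocol section 6, purpose (2), sets the aim: "the changes in blood pressure of different genotypes will be analyzed to determine whether genotype influence the blood pressure-decreasing response". Section 12, secondary outcome (3), repeats it for office blood pressure: "The changes in office blood pressure of different genotypes will be analyzed to determine whether genotype influence the blood pressure-decreasing response". Neither place names a test, a covariate, a genotype grouping or a time point.

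The genotyped set is one arm: "Only participants in the intervention group will have gene polymorphism testing at baseline". There are five loci: "Five single nucleotide polymorphisms (ACE, ACE2, AT1R, AT2R, Mas) will be genotyped".

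Section 18 is the only analysis text. It says "Continuous variables will be analyzed by *t* tests or Wilcoxon rank-sum tests" and, within groups, "The difference before and after treatment in each group will be determined using a paired *t* test". No regression or covariance model appears anywhere in the protocol.

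Baseline blood pressure is available. Under the main outcome: "The blood pressure will be measured at baseline, 4 weeks and 8 weeks after allocation". The trial process chart in section 4 agrees.

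**The concern.** A change score is negatively correlated with its own baseline whenever the correlation between the two visits is below 1 (equal variances assumed). People who happen to start high tend to fall further. The genotype groups are small subsets of one arm and are not formed by randomisation, so nothing holds their baselines together. A group that starts higher by chance will tend to show a larger fall, and under purpose (2) that could be read as sensitivity to auricular acupuncture.

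The second cost does not depend on any imbalance. When the correlation is moderate, the change score is a noisier outcome than follow-up blood pressure adjusted for baseline. In a comparison with about 32 patients, that loss matters.

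The genotype question is one of only two stated research purposes. It is still a secondary analysis, and the responder main outcome and its sample size are untouched.

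**Working it through.** **Inputs from the protocol.** 40 per group and 20% dropout (section 9), so 40 × 0.8 = 32 genotyped completers. Section 9 also gives "Setting an α-value of 0.05 and a β-value of 0.10" and response rates of 28% and 0%.

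**The plan's own figure.** The section 9 formula with mean proportion 0.14 and two-sided α gives 32.27, rounded up to 33 per group. Then 33 × 1.2 = 39.6, so 40, while 33/0.8 = 41.25 would give 42. The stated 40 is therefore reproduced to within 2 patients. It concerns the responder outcome. The protocol gives no power for the genotype comparison.

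**Assumptions.** The protocol gives no blood pressure SD, no baseline to week-8 correlation (ρ) and no genotype frequencies. I take equal SD σ at both visits, ρ = 0.5 with a range of 0.3 to 0.7, and two illustrative two-group splits of 32: 8 v 24 and 16 v 16.

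**Precision.** The variance of the change is 2(1−ρ)σ². The residual variance after baseline adjustment is (1−ρ²)σ². The ratio is (1+ρ)/2.

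| ρ | Variance ratio, adjusted/change | Share of a baseline gap passed into change, 1−ρ |
|---|---|---|
| 0.3 | 0.65 | 0.7 |
| 0.5 | 0.75 | 0.5 |
| 0.7 | 0.85 | 0.3 |

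Power (noncentral t, two-sided 5%) for a true genotype difference of 0.8σ:

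- 8 v 24, ρ = 0.5: √(1/8 + 1/24) = 0.408. The change score has SD σ, so the noncentrality is 0.8/0.408 = 1.96 and power is 47%. With adjustment it is 1.96/√0.75 = 2.26 and power is 59%.
- 16 v 16, ρ = 0.5: 59% rises to 71%.
- At 8 v 24 the gain is about 15 points at ρ = 0.3 and about 7 at ρ = 0.7.

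Allowing for estimation of the slope, the adjusted figures at ρ = 0.5 become 57.5% and 70%, so the gain is 10 to 11 points.

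**Chance baseline gap.** At 8 v 24 one standard error of the baseline gap is 0.41σ. A gap of 5 mmHg shifts the difference in change by 5 × (1−ρ) = 2.5 mmHg (3.5 at ρ = 0.3, 1.5 at ρ = 0.7).

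**Error rates with no genotype effect (simulation, 8 v 24).**

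- Over all data sets, the change-score test and the adjusted test both stay at 5%.
- A baseline gap above 1.5 standard errors occurs with probability 2 × (1 − Φ(1.5)) = 0.134. In those data sets the change-score test is falsely positive in about 12-13% at ρ = 0.5 (about 16% at 0.3, 9-10% at 0.7). The adjusted test stays near 5%.
- In the remaining 87% or so, the change-score test runs below nominal, at just under 4% for ρ = 0.5.

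**The reverse case.** Suppose a genotype raises blood pressure by the same amount at baseline and week 8 and has no effect on response. The change score is then unbiased, and the adjusted estimate carries (1−ρ) of the shift. At 8 v 24 and ρ = 0.5, a stable shift of 0.6σ gives the adjusted test about 12% false positives (17% at ρ = 0.3, 9% at 0.7), and a shift of 0.2σ gives about 6%. The change-score test stays at 5%.

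**The case against.** Three stronger readings are tempting, and the document supports none of them.

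*That the protocol expressly prescribes an unadjusted genotype test.* It does not. Secondary outcome (3) names no test, and section 18 never mentions genotype. The two-group tests there do not even fit three genotypes, although section 5 cites three for ACE (DD, ID, II). A statistical analysis plan, not available here, may add a model. What stands is narrower: the protocol makes the change the analysed variable, and its general rule for continuous variables offers only unadjusted tests. That is the natural reading, but it is a reading.

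*That the plan will produce too many falsely sensitive genes.* Averaged over possible baselines, the error is 5%. The raised figure applies to roughly one comparison in eight and is offset in the rest. The investigators will, however, hold one realised data set, and with five loci at least one gap above 1.5 standard errors has probability 1 − 0.866⁵ ≈ 0.51, if the loci are independent and each splits 8 v 24. The unadjusted result is then hard to interpret.

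*That baseline adjustment is the correct analysis and should decide the matter alone.* For non-randomised groups the two analyses answer different questions. The protocol's background holds that the renin-angiotensin system contributes to hypertension, so a genotype effect on baseline level is plausible. Adjustment would then create the kind of distortion it is meant to remove. This objection stands in full.

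It is also fair to say that adjustment does not cure two larger weaknesses: no genotyped controls, and five loci at P < 0.05 without correction (1 − 0.95⁵ = 23% chance of at least one false positive, if independent).

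**Conclusion.** The point holds as a loss of precision and of interpretability, not as an inflated overall error rate. Adjustment would leave 0.75 of the change-score variance at ρ = 0.5 (0.65 to 0.85 over the range shown). For a difference of 0.8σ that is worth about 10 to 12 points of power at ρ = 0.5. Even then power is only about 59-71%, so the analysis remains exploratory. The distortion from a chance baseline gap is real but conditional on the gap.

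These sizes rest on assumed ρ, equal SDs, an assumed effect size and illustrative genotype splits, since the protocol supplies none of them. The finding is a cheap improvement to a secondary analysis and does not affect the main outcome or the total of 80.

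**What to change.** In sections 12(3) and 18, prespecify for the intervention group a linear model of week-8 office diastolic pressure on genotype, with baseline diastolic pressure as covariate, and the same for systolic. Report each genotype difference with its 95% confidence interval. Beside it, report the unadjusted change by genotype, and tabulate baseline blood pressure by genotype. Label the analysis exploratory.

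State that no gene will be called sensitive from the adjusted estimate alone. Where the two estimates disagree, read the discrepancy against the baseline table: it may reflect a chance baseline gap or a stable genotype difference in level, and the data may not separate the two.

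The cost is a few sentences and one model per locus and pressure measure in the SPSS package already named, with no new data. The downside is two estimates that may differ. Fixing both in advance prevents a choice between them after the results are seen.
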